### Randomization

#### *Allocation unit*

Allocation will be done by clusters, and the randomizing unit will be the PHCCs.

#### *Sequence generation*

The 20 PHCCs will be allocated into intervention or control groups by using a stratified randomizing sequence by number of caregivers, generated by a computer (EPIDAT 3.1).

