## Methods/Design

### Study design

A community, controlled, multicentric clinical trial with randomized allocation by clusters and a 1-year follow-up period.

The intervention will be carried out by voluntary nurses with at least 3 years of experience in primary care, from 20 primary health care centers (PHCC) in the Community of Madrid (Spain).

The randomized unit will be the PHCCs (clusters). The analysis unit will be the caregiver (check-list cluster CONSORT in Additional file 1).

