### Sample size

Sample size has been calculated considering a relevant post-intervention average difference of 15 points between the intervention and control groups measured on the EQ-5D VAS, and a standard deviation of 25 (estimation obtained from Roset et al. [26]). This difference is equivalent to an effect size of 0.6.

Assuming an alpha error of 0.05 and a beta error of 20%, 44 caregivers are necessary for each group.

Since randomization is done by clusters, the sample size is adjusted in order to take into account the design effect. We have considered an intraclass correlation coefficient of 0.02 [27] and assumed an average cluster sample size of 15 caregivers. The design effect is 1.28. With these assumptions and expecting a 20% loss to follow-up after a 1-year period, the required sample size is 142 (71 caregivers per group).

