### Analysis

1. Descriptive analysis of each variable with its corresponding 95% confidence interval (CI). Tests for normality. Description of the profile of patients who abandon the study, and their reason for withdrawal.

2. Comparison of the group at the beginning of the trial for response variables, descriptive variables, and prediction factors. Bivariate, statistical, and other tests appropriate for the type of variable (qualitative or quantitative) will be used.

3. Analysis of primary outcome at the end of the intervention (0 month of follow-up period), and at 6 and 12 months after the intervention. The average change in EQ-5D VAS value before and after the intervention will be compared between the two groups by using parametric and/or non-parametric tests and the CI of the difference will be calculated. A mixed-effects regression model will be used to adjust by prognostic factors. Confounding factors or factors that may alter the recorded effect will be taken into account in this analysis.

4. Analysis of secondary outcome. For each of the secondary response variables, the variable outcomes will be compared based on the assigned group by calculating the difference of means or proportions of each variable, as well as CIs.

All statistical tests will be performed as intention-to-treat. The last and baseline observations carried forward will be used for missing data. Significance will be set at p < 0.05.

Researchers in charge of performing the analysis will not know which intervention has been assigned to each of the included patients.

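### Centres are randomised in strata of number of caregivers, but no stated analysis uses the stratum; if centre size is related to the VAS, a little precision is lost

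*Protocol article*

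**What the plan says.** Sequence generation: the 20 centres are allocated by computer with a "stratified randomizing sequence by number of caregivers". The number of strata and their cut-points are not given. Concealment of allocation places randomisation after the eligible caregivers have been chosen, so the stratum is known before allocation.

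Study design: centres are the randomised units, and "The analysis unit will be the caregiver".

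Analysis, item 3: mean change in VAS is compared between the two groups by parametric and/or non-parametric tests, with a confidence interval. The Abstract presents this comparison as the main analysis. Then: "A mixed-effects regression model will be used to adjust by prognostic factors". These factors are not listed. Item 4 gives the secondary outcomes differences of means or proportions with confidence intervals.

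The Variables section lists measurements on health professionals, dependent patients and caregivers. Centre size is not among them. The Discussion mentions modelling that allows for intracluster correlation but does not mention strata.

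**The concern.** Stratified allocation balances the arms on the stratum. If the stratum predicts the outcome, its variance drops out of the treatment contrast. A model with centre effects but no stratum term still counts that variance in the standard error. Its interval is then wider than the design warrants, and part of the benefit of stratifying is lost. With about 10 centres per arm, centre-level variance is worth controlling where that costs little. What is at stake is a small amount of precision and power, not the validity of the test.

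**Working it through.** **The plan's own figure.** Inputs from Sample size: a "relevant post-intervention average difference of 15 points between the intervention and control groups", "a standard deviation of 25", two-sided alpha 0.05 (sidedness not stated; two-sided reproduces the figure) and power 80%.

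- n per group = 2 × (25 × (1.960 + 0.842) / 15)² = 43.6, so 44, as stated.
- Design effect = 1 + (15 − 1) × 0.02 = 1.28.
- 44 × 1.28 / 0.8 = 70.4, so 71 per group and 142 in total. The stated size reproduces, and the fix does not change it.

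**Caregivers per centre.** The plan takes "an intraclass correlation coefficient of 0.02 [27] and assumed an average cluster sample size of 15 caregivers". With 142 caregivers in 20 centres the average is 7.1 enrolled, and 7.1 × 0.8 = 5.68 after the planned 20% loss. I use 5.68.

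**Variance of a centre mean** (ICC 0.02):

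- Total variance 25² = 625; between centres 0.02 × 625 = 12.5; within centres 612.5.
- 12.5 + 612.5 / 5.68 = 12.5 + 107.8 = 120.3.

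**Share removed if the stratum explains a fraction s of the between-centre variance:** s × 12.5 / 120.3. The SD cancels, so only the ICC, centre size and s matter.

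- s = 0: 0%.
- s = 0.5 (assumed): 6.25 / 120.3 = 5.2% of the variance, or about 2.6% of the standard error.
- s = 1: 12.5 / 120.3 = 10.4%, or about 5.3% of the standard error.
- With 7.1 per centre (no loss), s = 0.5: 6.25 / (12.5 + 612.5 / 7.1) = 6.25 / 98.8 = 6.3%.
- With ICC 0.05 (not in the document), s = 0.5: 15.625 / (31.25 + 593.75 / 5.68) = 15.625 / 135.8 = 11.5%.

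**Interval half-width**, 10 centres per arm, t × √(2 × variance / 10):

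- Stratum omitted, 18 df: 2.101 × √(2 × 120.3 / 10) = 10.31.
- Two strata fitted, s = 0.5, 17 df: 2.110 × √(2 × 114.1 / 10) = 10.08.
- Five strata fitted, s = 0.5, 14 df: 2.145 × √(2 × 114.1 / 10) = 10.25, so most of the gain is gone.

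**Simulation check.** Assumptions: two strata of 10 centres, 4 or 7 evaluable caregivers per centre (110 in total), true difference 15, SD 25, weighted centre-level analysis, 8000 runs per scenario. Each cell shows stratum omitted / stratum included.

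| ICC | s | Half-width | Coverage | Power |
|---|---|---|---|---|
| 0.02 | 0 | 10.33 / 10.38 | 95.5% / 95.6% | 80.7% / 80.4% |
| 0.02 | 0.5 | 10.36 / 10.11 | 95.6% / 95.2% | 81.9% / 83.2% |
| 0.02 | 1 | 10.33 / 9.81 | 96.1% / 95.2% | 82.4% / 84.9% |
| 0.10 | 1 | 12.18 / 9.54 | 98.7% / 95.3% | 71.8% / 87.1% |

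Omission never takes coverage below 95% here. The loss becomes material only if the ICC is well above 0.02 and centre size is strongly prognostic.

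**A plain caregiver-level test.** Such a test ignores centres. Its variance for an arm mean is 625 / 56.8 = 11.00, against a true 114.1 / 10 = 11.41 at s = 0.5, so its standard error is slightly too small. Ignoring clustering therefore acts in the opposite direction to omitting the stratum. The two cancel at s = 1 − 1/5.68 = 0.82.

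**The case against.** The strongest reply is that an article may leave the covariate list to a fuller document. The prognostic factors are not listed, and nothing excludes the stratum from the mixed model. That stands for the mixed model: a reader might infer that the stratum has been left out of it deliberately, and the text does not show this. It does not answer the primary two-group comparison or the secondary differences, which the article states in a form that has no place for a stratum. Nor do the recorded variables include centre size.

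A second reply is that no link between centre size and VAS is documented, and that balancing arm sizes is reason enough to stratify. That also stands, so the loss is conditional. Without a link, adding the term is marginally harmful (half-width 10.33 to 10.38).

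A reader might also infer that every stated test has standard errors that are too large and runs below its nominal level. The documents do not support that. It holds only for an analysis that allows for centres, and then only if the stratum is prognostic. In a simple caregiver-level test the missing allowance for clustering pulls the other way. That is a separate issue.

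**Conclusion.** The point holds as a minor, conditional one. The design stratifies by number of caregivers, the primary comparison and secondary differences do not use the stratum, and the mixed model does not name it. In a centre-aware analysis at ICC 0.02 with about 5.7 evaluable caregivers per centre, the cost is about 5% of the treatment-effect variance if the stratum explains half of the between-centre variance. It is essentially nothing if the stratum is unrelated to the VAS. In the simulation, even a stratum that explains all of it costs only about 5% of interval width and 2.5 points of power. The explained share and the number of strata are assumptions. It is also assumed that the sample-size ICC applies to the outcome as analysed; if baseline VAS already carries the centre-size effect, the gain shrinks. A reader might infer inflated type I error or invalid intervals from a mismatch between design and analysis. This omission produces neither: its error is on the conservative side.

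**What to change.** Make the primary analysis the mixed model with arm, baseline VAS, the randomisation stratum (number of caregivers) as a fixed effect, and a random centre effect. Use the same terms for the secondary outcomes, with the model suited to the type of outcome, and keep any simple two-group comparison as supportive. State the strata as they were used in the allocation.

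The stratum is known before allocation, so no new data are needed and the sample size stays at 142. The cost is one degree of freedom per stratum beyond the first, out of about 18 (20 centres less 2 arms). With two strata this is negligible. With many strata it would use up most of the small gain, so the number of strata should be stated when the term is fixed.

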#### *Concealment of allocation*

Randomization will be done in a centralized way by a researcher who does not participate in the study and is blind to the PHCC identity.

Main caregivers will be consecutively included in the study. During the home visit to the dependent patient, those caregivers meeting inclusion requirements for the trial will be informed of it and offered participation. If accepting to participate, they will be asked to fill in and sign the written consent and the meeting of all inclusion criteria, and no exclusion criteria, will be verified.

Randomization of PHCCs will be done once the caregivers eligible for the study have been chosen, so that recruitment by health professionals is not influenced by their allocation to a study group [28,29].

### Masking

It is not possible to mask the intervention in this type of trials. Post-intervention variables measurement will be performed by a group of nurses who will not know which group the caregiver belongs to. In the same way, the analysis will be done by professionals unaware of the allocation.

### The intervention

#### *Control group*

Standard clinical practice: the home consultation service to immobile patients from the *Cartera de Servicios estandarizados de Atención Primaria *[23] defines the care to be provided to dependent patients. For the caregiver, there is no formal care and their care needs are addressed individually.

#### *Intervention group*

Dependent patients will be given the care defined in the home consultation service to immobile patients from the *Cartera de Servicios estandarizados de Atención Primaria *[23].

In addition to assisting the caregivers in their eventual needs for care, they will be provided with the assistance defined in the CuidaCare intervention.

CuidaCare is a complex intervention that consists of the combination of several components aimed at improving the quality of life of caregivers. It has been designed by a multidisciplinary group of primary health care professionals, experts at nursing care and psychological approach to behavior.

It uses strategies to improve dealing with the role of a caregiver, training on health-related self-care and dependent patients' care, as well as emotional support.

As methodological support for its development, the recommendations of the NANDA-I have been used, which propose outcome criteria (NOC) and nursing interventions (NIC) to be employed in order to facilitate research approach for studying the main nursing diagnosis for main caregivers.

Figure 1 shows schematically the different components of both the control and the CuidaCare interventions [30].

**Figure 1 F1:**
[figure not shown]
Componets of CuidaCare complex intervention vs standard clinical practice.

Along the 10 programmed visits of the CuidaCare intervention, nurses allocated to this group will deal with the following content: health care system guidelines and caregiver support, nervousness and stress control, caregiver's self-care, self-esteem, self-learning, identifying sources of stress, dealing with problems, and improving communication skills.

### Variables

#### *Outcome variables*

The main outcome variable is quality of life perceived by the caregiver, expressed on the EQ-5D VAS [20,21]. This questionnaire comprises two sections: the VAS and the descriptive system EQ-5D Dimensions. In the VAS, subjects evaluate their own health condition on a scale ranging from 0 (worst imaginable health condition) to 100 (best imaginable health condition). The EQ-5D Dimensions system contains 5 questions where 5 dimensions of HRQL (Mobility, Self-Care, Usual Activities, Pain/Discomfort, Anxiety/Depression) are evaluated. Each question has 3 possible answers ranging from 1 (I do not have difficulties) to 3 (I have many difficulties).

#### *Health professional variables*

• Socio-demographic: sex and age.

• Years of experience in primary care and specific training in providing assistance to caregivers.

#### *Dependent patient variables*

• Socio-demographic: sex, age, marital status, and educational level.

• Degree of dependency on the BADL (Barthel scale) and on instrumental activities (Lawton and Brody scale), degree of cognitive deterioration (Pfeiffer's test), and time since first inclusion in the supplied service of immobile patient care and related co-morbidity.

#### *Caregiver variables*

• Socio-demographic: sex, age, marital status, educational level, and socioeconomic level.

• Kinship with the care-receiver and number of household members.

• Time (years) since first functioning as a caregiver and presence or absence of formal support (defined as professional or institutional received help).

• EuroQol-5D [21]: EQ-5D Dimensions, EQ-5D Index (index of preference-based measurements or utilities).

• Presence or absence of care problems related to the role as caregiver (nursing diagnosis NANDA-I), degree of caregiver effort (Zarit's scale), signs of depression (Yesavage's test), degree of anxiety (Goldberg's scale), and perception of family function (Apgar family test).

### Data collection method

Information will be collected via a clinical interview and data will be recorded in an electronic data collection notebook specifically designed for this trial. Variables will be collected during 4 visits: at the beginning of the trial, at the end of the intervention, and at 6 and 12 months after the intervention. The timing for the data collection is shown in Table 1.

**Table 1 T1:** Procedures to be followed and information to be recorded at each patient’s visit

	
Step 1	Recruitment of caregivers
	- Presentation/information about the trial
	- Invitation to participate
	- Checking inclusion/exclusion criteria
	- Signing of informed consent
	- Collection of sociodemographic variables (dependent patient and caregiver)
Step 2	Primary health care center randomization
Step 3	Base-line visit
	Collection of variables on:
	- Dependent Patient: degree of cognitive deterioration and dependency level.
	- Evaluation of formal support.
	- Caregiver: self-perceived quality of life, degree of burden, evaluation of anxiety/depression degree, Apgar family test, and nursing diagnosis.
Step 4	Intervention period (duration of 6 months)

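### Centres are randomised before the baseline EQ-5D VAS is taken, and no text keeps allocation from nurses or caregivers until it is recorded, so the change-score primary outcome is open to bias

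*Protocol article*

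**What the plan says.** Table 1 (Data collection method) numbers the steps. Step 1 is recruitment: information, eligibility, consent and "Collection of sociodemographic variables (dependent patient and caregiver"). Step 2 is "Primary health care center randomization". Step 3 is the "Base-line visit", which records, among other things, "Caregiver: self-perceived quality of life, degree of burden, evaluation of anxiety/depression degree, Apgar family test, and nursing diagnosis", together with the patient's dependency and cognitive status and formal support. The VAS does not appear before Step 3.

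On blinding, the Masking section says "It is not possible to mask the intervention in this type of trials" and then "Post-intervention variables measurement will be performed by a group of nurses who will not know which group the caregiver belongs to". It has no matching statement for baseline.

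The Concealment of allocation section says "Randomization of PHCCs will be done once the caregivers eligible for the study have been chosen". The reason it gives is that recruitment should not be influenced by allocation.

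Item 3 of the Analysis section defines the primary comparison: "The average change in EQ-5D VAS value before and after the intervention will be compared between the two groups". A mixed-effects model adjusting for prognostic factors is added, but the factors are not named.

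**The concern.** Randomising after the caregivers have been chosen protects against selective recruitment. It does not protect the baseline measurement, which comes one step later. The VAS is a subjective 0 to 100 self-rating taken in a clinical interview, in a trial whose arms cannot be masked. A caregiver or nurse who knows whether ten structured visits are coming may rate or record the starting point differently.

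Baseline is one of the two components of the change score, so this is not a side issue. The Discussion claims blind evaluation of the outcome, but the stated blinding covers only the post-intervention component.

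Two lesser consequences follow from the same order. Any Step 3 measure used as a covariate would be a post-randomisation variable. A caregiver lost between Steps 2 and 3, if there are any, would have no baseline value, so no change score could be formed and the baseline-carried-forward rule would have nothing to carry.

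**Working it through.** **Inputs from the Sample size section.** Difference 15 points; SD 25; alpha 0.05 (taken as two-sided; the article does not say); power 80%; intraclass correlation 0.02; average cluster size 15; loss 20%; 71 per group; 20 centres (Study design).

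**Reproducing the plan's figure.**
- n per group = 2 × (1.96 + 0.8416)² × 25² / 15² = 43.6, rounded up to 44.
- Design effect = 1 + (15 − 1) × 0.02 = 1.28.
- 44 × 1.28 = 56.32; 56.32 / 0.80 = 70.4, rounded up to 71 per group, 142 in total.

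The stated figures reproduce.

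**Standard error of the between-group difference.** The SD of 25 is applied to the change score. That is an assumption, and it is exact if each visit has SD 25 and the baseline/follow-up correlation rho is 0.5. After loss, 71 × 0.80 = 56.8 per group.
- Planned cluster size 15: effective n = 56.8 / 1.28 = 44.4; SE = 25 × √(2 / 44.4) = 5.31.
- Cluster size implied by 20 centres after loss, 142 × 0.80 / 20 = 5.68: design effect = 1 + 4.68 × 0.02 = 1.094; effective n = 51.9; SE = 4.91.

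**Unadjusted change score.** A spurious baseline difference b between arms enters the contrast in full. With no true effect, the two-sided rejection rate is Φ(−1.96 − b/SE) + 1 − Φ(1.96 − b/SE). The values of b are assumed.

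| b (points) | SE 5.31 | SE 4.91 |
|---|---|---|
| 0 | 5% | 5% |
| 3 | 8.7% | 9.4% |
| 5 | 15.6% | 17.5% |

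If SD is 25 at each visit and rho runs from 0.3 to 0.7, the change-score SD is 25 × √(2(1 − rho)), that is 29.6 down to 19.4. At SE 5.31 rescaled accordingly, the 5-point figure then runs from 12.5% to 22.9%.

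**Baseline VAS as a covariate.** With equal SDs the bias becomes about rho × b and the SE becomes SE × √(1 − rho²).

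| rho | bias for b = 5 | rate, SE 5.31 | rate, SE 4.91 |
|---|---|---|---|
| 0.3 | 1.5 | 6.0% | 6.2% |
| 0.5 | 2.5 | 8.5% | 9.1% |
| 0.7 | 3.5 | 15.2% | 17.0% |

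For b = 3 the rates are 5.4% to 8.6% at SE 5.31. Adjustment reduces the bias but does not remove it.

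**Shift in the other direction.** At SE 5.31, power for a true 15 points in the unadjusted comparison is 81%. It falls to 62% if 3 points are lost and to 47% if 5 points are lost.

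**The case against.** The strongest reply is that knowledge of allocation at baseline is inferred. The article does not say who takes the baseline VAS or when a centre's allocation is released. Randomisation is central, by someone outside the study who is blind to centre identity, and drawing a sequence is not the same as disclosing it. The full protocol may settle both points. A reader might therefore infer from Table 1 that baseline nurses and caregivers do know the arm; the article does not support that. What stands is that the printed order allows it and no statement rules it out.

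Three further inferences go too far:
- That covariate adjustment as a whole rests on post-randomisation variables. The sociodemographic variables of patient and caregiver are collected at Step 1, before randomisation. Only Step 3 measures are affected, and only if they are used.
- That the bias always passes through in full. This is true of the raw change score. If baseline VAS is in the mixed model, which is not stated, the bias shrinks to about rho × b.
- That the intention-to-treat set will lose caregivers differentially. No interval between Steps 2 and 3 is given, no loss there is described, and losses with their causes are to be recorded. This remains hypothetical.

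It is also fair to say that the 3- and 5-point shifts have no source in the article. They show sensitivity and are not an estimate.

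**Conclusion.** The point holds as a conditional risk to the primary outcome. The order of steps and the limit of the blinding promise are both explicit. Together they leave a self-rated baseline unprotected against knowledge of allocation. Whether bias would occur, how large it would be and in which direction cannot be learned from the article.

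The illustrative error rates depend on assumed shifts, an SD of 25 for the change score, a normal approximation and two-sided testing. A 5-point shift is one third of the 15-point target, so a modest reporting difference would matter. A larger sample would not remove such a bias, and baseline adjustment would remove only part of it. Prevention has to come before the first baseline visit.

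**What to change.** In Table 1, place the baseline visit before centre randomisation, and state that baseline is completed and locked for all consented caregivers before the centres are randomised. Equivalently, keep the printed order but state that no centre's allocation is released to its nurses or caregivers until all its baseline records are locked. Blinding only the baseline interviewer would not be enough, because the VAS is self-rated and the caregiver could still know the arm.

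The cost is small. Caregivers are already identified and consented before Step 2, so no new visit is needed and the sample size stays at 142. The baseline value will be somewhat older when the intervention starts, which a short window before randomisation would limit. The first option also needs coordination across centres, since randomisation is stratified by number of caregivers and would wait for the last baseline to be locked. The second largely avoids that wait and needs only a clarifying sentence and control over release.
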